#### Sample size and statistical considerations

A total of 176 patients (88 per arm) are required to prove that the 95% lower limit of one-sided CI will be above the non-inferiority limit of − 1.5 ESS points difference (standard deviation of 4), with 80% of power. A previous RCT used a non-inferiority margin of 2 ESS points and 80% as minimal power to compare pitolisant versus modafinil in patients with narcolepsy [30]. As the TMC study will not test drugs, we decided to adopt a stricter margin (1.5 ESS points). The standard deviation value (±4) was based on the Italian validation study of ESS [28]. Considering 15% of dropouts, the sample was enlarged to 202 (101 per arm). Repeated measures ANOVA will be used to compare EDS between groups at baseline and after 1-yr of follow-up.

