#### Population, intervention and procedures

Adolescents (≥14 years old) and adults with a diagnosis of narcolepsy according to ICSD-3 [1] criteria soon after the diagnosis (“incident”) or with established diagnosis (“prevalent” subjects) in charge at the CN of the IRCCS Istituto delle Scienze Neurologiche di Bologna, Italy, and able to provide consent are eligible. Exclusion criteria are the following: major psychiatric disorders; inability to read, write, or using a tablet; and no Internet access.

Patients who provide informed consent will undergo the following baseline in-person assessment by different experts through standardized tools (see Table 1):
sleep assessment;endocrine/metabolic assessment, with measurement of weight, height, waist circumference, blood pressure, heart rate; anda counselling session on the psychosocial impact of narcolepsy.

Patients will also be requested to complete a physical activity questionnaire [29], and to provide a 24-h food diary. In addition, a blood sample will be collected for a metabolic (lipid and glucose profile, and thyroid function) evaluation.

After baseline procedures, patients will be consecutively randomly allocated in 1:1 ratio either to TMC via videoconference or to standard in-person follow-up in-office visits (control arm). The randomization list (stratified for three groups: children, adults with incident condition, adults with prevalent condition) and allocation will be generated by an automatic web-based system after inclusion.

The TMC will consist of scheduled TVs through a tablet and remote data collection through an ad hoc designed electronic case report form (e-CRF). A videoconference service will be used. The TV will be performed aiming at assessing the patient’s condition, and his/her need/response to treatments. TVs will end with therapeutic prescriptions according to usual practice, until the next follow-up TV. A formal report of the sleep assessment through TV will be sent by mail to the patient. The standard in-person follow-up care consists in scheduled (3–6-9 months) usual in-office visits, performing the same assessments, data collection and therapeutic prescriptions according to usual practice. The scheduling of follow-up TVs or in-person visits (at 3–6-9 months) will be based on the patient’s condition and needs (see Table 1).

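### The 80% power is not tied to the effect that the repeated measures ANOVA will test; under the usual arm-by-time test it depends on an unstated correlation, and a baseline-adjusted 12-month comparison would remove that dependence

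*Protocol article*

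**What the plan says.** All the figures stand in the protocol article, TMC study, Sample size and statistical considerations.

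- Criterion: the "95% lower limit of one-sided CI will be above the non-inferiority limit".
- Margin: "we decided to adopt a stricter margin (1.5 ESS points").
- Variability and power: "ESS points difference (standard deviation of 4), with 80% of power".
- Source of the SD: "The standard deviation value (±4) was based on the Italian validation study of ESS [28"].
- Result: "A total of 176 patients (88 per arm) are required", enlarged to 202 for dropout.
- Analysis: "Repeated measures ANOVA will be used to compare EDS between groups at baseline and after 1-yr of follow-up".

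The section does not say whether SD 4 describes a single score or a change. It gives no baseline to 12-month correlation, and it does not say which ANOVA effect supplies the difference and its confidence limit.

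Under Population, intervention and procedures, the trial takes patients "soon after the diagnosis (“incident”) or with established diagnosis (“prevalent” subjects"). Table 1 schedules the ESS at month 0 and month 12 for both groups.

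**The concern.** The sizing and the analysis stand side by side in one section, but nothing connects them. The sizing has one SD and no correlation. The analysis has two correlated measurements per patient and can yield three different arm effects:

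- **Arm-by-time term.** This is the usual test of treatment in a two-time repeated measures ANOVA. It is equivalent to comparing change scores, so its precision depends on r.
- **Arm main effect.** This averages the baseline score, which randomised care cannot affect, with the 12-month score.
- **Between-arm contrast at 12 months.** This matches the sizing formula but makes no use of the baseline score.

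The choice matters because this is the trial's primary non-inferiority question. With the first effect and a low r, a truly non-inferior televisit arm could miss the margin much more often than the planned one time in five. With the second, a real 12-month deficit would be diluted, which in a non-inferiority trial favours a false claim of success.

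**Working it through.** **Inputs.** From the sample size section: margin 1.5, SD 4, one-sided 5%, power 80%, 88 per arm. Assumptions, since the article is silent: true difference 0, SD 4 is the single-score SD at both times, and r lies between 0 and 0.7.

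**Reproducing the plan's figure.** n per arm = 2 × (1.645 + 0.8416)² × 4² / 1.5² = 87.93, so 88. In reverse, SE = 4 × √(2/88) = 0.603, and power = Φ(1.5/0.603 − 1.645) = 80.0%. A noncentral t calculation gives 79.8%. A one-sided 2.5% level would need 112 per arm, so one-sided 5% was used. The plan's number is correct for the formula used.

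**Arm-by-time (change) test.** SD of change = 4 × √(2(1 − r)), which equals 4 at r = 0.5 and exceeds 4 below it. Power = Φ(1.5/(SD × √(2/88)) − 1.645).

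**12-month ESS adjusted for baseline.** Residual SD = 4 × √(1 − r²), with the same power formula.

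| r | SD of change | Power, change | n per arm for 80%, change | Adjusted SD | Power, adjusted |
|---|---|---|---|---|---|
| 0 | 5.66 | 55% | 176 | 4.00 | 80% |
| 0.2 | 5.06 | 63% | 141 | 3.92 | 81% |
| 0.3 | 4.73 | 68% | 124 | 3.82 | 83% |
| 0.4 | 4.38 | 73% | 106 | 3.67 | 86% |
| 0.5 | 4.00 | 80% | 88 | 3.46 | 89% |
| 0.6 | 3.58 | 87% | 71 | 3.20 | 93% |
| 0.7 | 3.10 | 94% | 53 | 2.86 | 97% |

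The adjusted analysis is never less precise than the change analysis: 1 − r² = (1 − r)(1 + r), and 1 + r cannot exceed 2. It is also never less precise than the raw 12-month comparison, because 1 − r² cannot exceed 1.

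**Unadjusted 12-month contrast.** SD 4 whatever r is, so 80% throughout.

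**Arm main effect.** With arms equal at baseline, a true 12-month deficit of 1.5 appears as (0 + 1.5)/2 = 0.75. The SD of a patient's two-time mean is 4 × √((1 + r)/2), which is 3.46 at r = 0.5, so SE = 3.46 × √(2/88) = 0.522. Judged against an unchanged margin of 1.5, non-inferiority would be declared with probability Φ(0.75/0.522 − 1.645), about 42%, when the true 12-month deficit sits exactly at the margin. The intended rate is 5%.

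**The case against.** The strongest reply is that nothing is arithmetically wrong and no shortfall is demonstrated. Four parts of it stand.

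- **The tested effect is not named.** A reader might infer that the plan commits to analysing change. The sentence can equally be read as comparing the arms at each time, and a 12-month contrast from the same model keeps 80% at any r.
- **The SD's meaning is not stated.** A validation study suggests a single-score SD, but that study is not at hand. The formula returns 88 whether 4 is the SD of a score or of a change, so reproducing 88 does not settle it.
- **The correlation is unknown.** A reader might infer that the trial is underpowered. At r = 0.6 or 0.7 it would exceed 80% even on the change reading. Newly diagnosed patients starting treatment could lower r, while established patients in stable follow-up could raise it. The article gives no ESS data for either group. Randomisation is stratified by incident and prevalent status in adults, and including stratum in the model could absorb mean shifts between strata.
- **The r = 0.5 threshold is conditional.** It needs equal SDs at both times and an unadjusted change contrast.

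It can also be said that a condensed article leaves model terms to the full protocol or analysis plan. That is fair for omitted detail. Here, however, the article itself fixes both a power figure and a named method, and on its most usual reading the method does not carry that power without a further assumption. That part of the point is not answered.

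**Conclusion.** The point holds as a missing link between the sizing and the analysis. It is neither a wrong sample size nor a proven loss of power. The 88 per arm is right for a two-sample comparison with SD 4. Whether 80% also belongs to the repeated measures ANOVA depends on which effect is tested, what SD 4 measures and, for the arm-by-time term, on r. On that reading, with SD 4 as the single-score SD at both times, power runs from about 63% at r = 0.2 to 94% at r = 0.7 and crosses 80% at about r = 0.5. The documents do not support going further, to a statement that power is below 80% or that the stated power belongs to an analysis other than the one planned.

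The change is worth making whichever reading was meant. The baseline-adjusted 12-month comparison is at least as precise as both the change analysis and the raw 12-month contrast, and it rules out the diluted main effect. Its floor of about 80% rests on SD 4 at 12 months, a true difference of 0, 88 evaluable patients per arm and the large-sample formula.

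**What to change.** Replace the repeated measures ANOVA sentence with a primary estimate: the between-arm difference in ESS at 12 months, adjusted for baseline ESS, from an ANCOVA or an equivalent mixed-model contrast. State that its one-sided 95% confidence limit is compared with the 1.5-point margin, and that 88 per arm gives about 80% power or more at SD 4, whatever the correlation.

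If a change analysis is kept, name the arm-by-time contrast as the tested effect, state the SD of change or the assumed r, and give power over the full plausible range, including values of r above 0.5 as well as below.

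The cost is wording only. Baseline ESS is already collected, and no extra patients or visits are needed.

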**Methods:**

TENAR is a two-part project, including: 1. a cross-sectional study (involving 250 children and adults with suspected narcolepsy) evaluating the accuracy of Teletriage (i.e., a synchronous live interactive sleep assessment through a Televisit) for narcolepsy diagnosis compared to the reference standard; and 2. a two-arm, parallel, open randomized controlled trial (RCT) to demonstrate the non-inferiority of the multidisciplinary care of narcolepsy through Televisits versus standard care. In this RCT, 202 adolescents (> 14 y.o.) and adults with narcolepsy will be randomly allocated (1:1 ratio) either to Televisits via videoconference or to standard in-person outpatient follow-up visits (control arm). The primary outcome is sleepiness control (according to the Epworth Sleepiness Scale). Secondary outcomes are other symptoms control, compliance with treatment, metabolic control, quality of life, feasibility, patient and family satisfaction with care, safety, and disease-related costs. At baseline and at 12 months, patients will undergo neurologic, metabolic, and psychosocial assessments and we will measure primary and secondary outcomes. Primary outcomes will be also measured at 6 months (remotely or in person, according to the arm).

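### The 15% dropout allowance is slightly too small: 202 randomised patients leave about 172, not the required 176, and power is about 79% rather than 80%

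*Protocol article*

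**What the plan says.** The protocol article gives the calculation in one paragraph, under Sample size and statistical considerations for the Tele-multidisciplinary care (TMC) study.

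- Evaluable number: "A total of 176 patients (88 per arm) are required to prove" the non-inferiority claim, "with 80% of power".
- Criterion: the "95% lower limit of one-sided CI will be above the non-inferiority limit".
- Margin and spread: a "non-inferiority limit of − 1.5 ESS points difference (standard deviation of 4"). On the source of the spread: "The standard deviation value (±4) was based on the Italian validation study of ESS".
- Dropout allowance: "Considering 15% of dropouts, the sample was enlarged to 202 (101 per arm").

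The Population, intervention and procedures section sets equal allocation: "patients will be consecutively randomly allocated in 1:1 ratio". The abstract repeats the total as "202 adolescents" and adults. The article prints no formula for the dropout step and does not state the true difference assumed.

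**The concern.** The enlargement has one purpose: to leave the necessary number of patients once the expected losses have occurred. A dropout rate is ordinarily a share of those randomised, so the evaluable number should be divided by 1 − 0.15. The printed figures look like multiplication by 1 + 0.15, which always falls short.

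At stake is whether the evaluable number, the dropout rate and the randomised number given in that paragraph agree with one another. The randomised total is also the headline sample size in the abstract. The 88 per arm has almost no slack, so any shortfall takes the plan below its own power target, if only slightly.

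**Working it through.** **Inputs**, all from the TMC sample-size paragraph unless marked:

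- margin 1.5 ESS points
- SD 4
- one-sided α = 0.05 (z = 1.645)
- power 80% (z = 0.8416)
- 1:1 allocation (Population, intervention and procedures section)
- dropout 15%
- 176 evaluable and 202 randomised patients
- true difference 0 (assumption; not stated)

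**Step 1: reproduce the evaluable number.**

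n per arm = 2 × (z₁₋α + z₁₋β)² × SD² / margin² = 2 × (1.645 + 0.8416)² × 16 / 2.25 = 87.93, rounded up to 88.

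This gives 176 in total, as printed. One-sided α = 0.025 would give 112 per arm, so 0.05 is the level used. The match also supports the assumed true difference of 0. Normal-approximation power at 88 per arm is 80.03%.

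**Step 2: identify the dropout step.**

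| Rule | Per arm | Total |
|---|---|---|
| Multiply by 1.15 | 88 × 1.15 = 101.2 | 176 × 1.15 = 202.4 |
| Divide by 0.85 | 88 / 0.85 = 103.5 | 176 / 0.85 = 207.1 |
| Printed | 101 | 202 |

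The printed figures match multiplication by 1.15 with the fraction rounded down. Division by 0.85, rounded up within each arm, gives 104 per arm and 208 in total. As a check, 104 × 0.85 = 88.4.

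**Step 3: what remains of 202 at 15% loss.**

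202 × 0.85 = 171.7, or 85.85 per arm. The shortfall is 176 − 171.7 = 4.3 evaluable patients, or 208 − 202 = 6 randomised patients (6 / 202 = 3.0%).

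**Step 4: power at that number.**

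Power = Φ(margin / (SD × √(2/n)) − 1.645)

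At n = 85.85: Φ(1.5 / (4 × √(2/85.85)) − 1.645) = 0.792.

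| Evaluable per arm | Power, normal approximation | Power, noncentral t |
|---|---|---|
| 85 | 78.8% | 78.5% |
| 86 | 79.2% | 78.9% |
| 88 | 80.0% | 79.8% |

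**Step 5: the dropout that 202 does cover.**

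1 − 176/202 = 26/202 = 12.9%.

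**The case against.** The strongest reply is that the article attaches 80% power to 176 patients, which is correct, and never says in so many words that 202 leaves 176. Read as enlarging 176 by 15%, the sentence gives 202.4 and the number fits. On that reading, though, the 26 added patients are 12.9% of those randomised, and the article does not say that its dropout rate is a share of completers. The multiplication rule is indeed an inference, since no formula is printed. The subtraction in step 3 does not depend on that inference.

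A second reply is that Table 1 separates patients who drop out fully from those who only change procedure. If the 15% covered both, fewer would lose their ESS data and the gap would shrink or vanish. The paragraph does not say so. What stands is that the 79.2% assumes all 15% are lost to the primary analysis.

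A third reply, on size, stands in full. The same power loss would follow if the SD were 4 × √(88/85.85) = 4.05 instead of 4, a 1.2% change in a rounded planning value. A reader might infer from the shortfall that the trial is underpowered or that its 80% claim has failed. A drop of about 0.8 percentage points does not support that.

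A reader might also infer that the primary analysis, because it uses baseline values, makes good the loss. The article does not support this either. It names only repeated measures ANOVA on baseline and one-year values and gives no correlation between them. If the contrast is a change score, its variance is 2 × SD² × (1 − ρ), which is below SD² only when ρ exceeds 0.5. No such gain should be claimed.

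**Conclusion.** The point holds as a minor arithmetic error. The evaluable number, dropout rate and randomised number do not agree as printed: at 15% loss, 202 patients leave about 172, roughly 4 fewer than the paragraph calls necessary. Correct inflation gives 208, which is 6 more.

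Power at 15% loss is about 79.2%, against 80.0% at 88 per arm. This rests on a true difference of 0, SD 4, one-sided α = 0.05 and the loss of every dropout from the primary analysis. The base calculation of 176 is sound, and the trial is not materially underpowered. The planning statement needs correcting; the design does not.

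**What to change.** Keep 202 and restate the sentence, for example:

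*202 patients (101 per arm) retain 176 evaluable patients and 80% power with up to 12.9% dropouts; with 15% dropouts about 172 remain and power is about 79%.*

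State beside it that the calculation takes the true difference as 0 and counts every dropout as lost to the primary analysis. Do not add a claim that the choice of analysis recovers the loss unless a baseline-to-12-month correlation is given to support it.

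The cost is one corrected sentence and a slightly less favourable planning figure, with no extra patients. If the sponsor prefers to keep both the 15% and the 80%, the figure is 208 (104 per arm), which costs 6 more patients. The size of the gap does not require this.

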### Tele-multidisciplinary care (TMC) study

#### Study design and outcomes

The TMC study is a 12-month, two-arm, parallel, open RCT aiming to demonstrate the non-inferiority for EDS control of the multidisciplinary care of narcolepsy through TVs versus standard in-person follow-up care (Fig. 1). Primary outcome is EDS control (according to the Epworth Sleepiness Scale, ESS [28]). Secondary outcomes are the following: other symptoms control, compliance with treatment, metabolic control, quality of life, feasibility, patient and family satisfaction with care, safety, and disease-related costs. Primary and secondary outcomes, and related measures and timepoints for data collection are summarized in Table 1.

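### The only analysis named for the primary ESS outcome, a repeated measures ANOVA, is not tied to the non-inferiority limit, and the effect to be judged is left open

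*Protocol article*

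**What the plan says.** The protocol article describes the TMC study, under Study design and outcomes, as a trial "aiming to demonstrate the non-inferiority for EDS control", with the ESS as the primary outcome measure.

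The TMC section on sample size and statistical considerations gives a decision criterion. The trial is sized to show that "the 95% lower limit of one-sided CI will be above the non-inferiority limit of" −1.5 ESS points, "with 80% of power". It gives the size as follows: "A total of 176 patients (88 per arm) are required". On the variability it says: "The standard deviation value (±4) was based on the Italian validation study of ESS".

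The same paragraph ends with the only analysis named for ESS: "Repeated measures ANOVA will be used to compare EDS between groups at baseline and after 1-yr of follow-up". It does not say which effect of that model is meant: the group main effect, the group-by-time interaction, or a contrast at 12 months. It does not mention the margin again.

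**The concern.** A non-inferiority claim needs one stated estimate, with a confidence limit compared with the margin. The standard output of a repeated measures ANOVA is a set of F-tests of zero difference, and a non-significant F-test is not evidence of non-inferiority. A confidence limit can be taken from the model, but different effects in it estimate different quantities.

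This matters because the baseline ESS is collected before allocation (Population, intervention and procedures), so the expected difference between arms at baseline is zero. Any effect that averages baseline with 12 months pulls a real 12-month harm towards zero, and in a non-inferiority trial that favours the claim. An effect based on change does not dilute the harm, but its precision depends on the correlation between the two measurements, which the sample size did not consider. What is at stake is the planned 5% error under one reading and the planned 80% power under another.

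**Working it through.** **Inputs from the article:** margin 1.5 ESS points, SD 4, one-sided 5%, power 80%, 88 evaluable patients per arm, baseline measured before randomisation.

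**Assumptions:** SD 4 at both times, normal approximation, and a baseline/12-month correlation ρ of 0.3, 0.5 or 0.7. The article gives no value for ρ. Harm means the excess of TMC over control at 12 months, in the direction of worse sleepiness.

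**Step 1. Reproduce the plan's figure.** With no true difference, n per arm = 2 × (1.645 + 0.842)² × 4² / 1.5² ≈ 87.9, rounded up to 88, or 176 in all. This matches. The size therefore rests on a simple comparison of two means at one time, with SE = 4 × √(2/88) = 0.603. With that SE, the chance of passing is 5.0% at a true harm of 1.5 and 80.0% at no harm.

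**Step 2. What each candidate estimate measures.**

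- Group main effect over the two times: (baseline difference + 12-month difference)/2. Its expectation is harm/2, with SE = 0.603 × √((1+ρ)/2).
- Group-by-time contrast (difference in change): expectation is the full harm, with SE = 0.603 × √(2(1−ρ)).
- ANCOVA on 12-month ESS adjusted for baseline: expectation is the full harm, with SE = 0.603 × √(1−ρ²).

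In each case P(non-inferiority declared) = Φ((1.5 − expected effect)/SE − 1.645).

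**Step 3. Results at 88 per arm.**

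| Estimate set against 1.5 | Quantity | ρ = 0.3 | ρ = 0.5 | ρ = 0.7 |
|---|---|---|---|---|
| Group main effect | SE | 0.486 | 0.522 | 0.556 |
| | Passes at true harm 1.5 | 45.9% | 41.7% | 38.4% |
| Group-by-time | SE | 0.714 | 0.603 | 0.467 |
| | Passes at true harm 1.5 | 5.0% | 5.0% | 5.0% |
| | Power at no harm | 67.6% | 80.0% | 94.1% |
| Baseline-adjusted ANCOVA | SE | 0.575 | 0.522 | 0.431 |
| | Passes at true harm 1.5 | 5.0% | 5.0% | 5.0% |
| | Power at no harm | 83.2% | 89.0% | 96.7% |

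Example for the main effect at ρ = 0.5: (1.5 − 0.75)/0.522 − 1.645 = −0.21, and Φ(−0.21) ≈ 0.42. The error for this effect returns to 5% only when harm/2 = 1.5, that is, at a true harm of 3.0 points. The margin is then in effect doubled.

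For the group-by-time contrast, √(2(1−ρ)) exceeds 1 whenever ρ is below 0.5. Its SE is then larger than the 0.603 used for sizing, and power falls below 80%. For ANCOVA, √(1−ρ²) never exceeds 1, so power is never below the planned value.

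**Step 4. Simulation check.** In 20,000 simulated trials with a true harm of 1.5, the main effect passed in 40.8% (ρ = 0.5) and 37.3% (ρ = 0.7). The group-by-time contrast and the plain 12-month difference passed in about 5%.

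**The case against.** The strongest reply is that the plan already contains the decision rule. The one-sided limit and the ANOVA stand in the same paragraph, so the natural reading is that the model supplies the estimate and the limit supplies the decision. A comparison of groups before and after is most naturally the group-by-time contrast, which holds 5% error. A condensed article may also leave the exact contrast to a full protocol or SAP that is not shown.

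Much of this stands, and it rules out three stronger readings.

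- A reader might infer that the plan has no non-inferiority criterion. It has one, and the sample size reproduces from it exactly.
- A reader might infer that the planned analysis halves any harm, so that an inferior TMC would be declared non-inferior. That holds only for the group main effect, which the article does not name.
- A reader might infer that a non-significant F-test would be taken as non-inferiority. No section says so, and the stated limit points the other way. Nor does the text show that a separate significance test at baseline is meant to answer a trial question.

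What the reply does not remove is the gap itself. The article chose to state an analysis for its primary outcome, and that analysis is not connected to the criterion given a few lines above it. The reading most favourable to the plan also fails to match the sample size, since its power is about 68% at a correlation of 0.3.

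**Conclusion.** The point holds in a conditional form. The stated criterion and the only named ESS analysis are not linked, and the model's standard tests are tests of equality. If the limit came from the group main effect, the false non-inferiority rate at a true harm of 1.5 would be about 46%, 42% or 38%, against 5% planned. If it came from the group-by-time contrast, the error would be as planned but power would be about 68%, 80% or 94%. Both sets of figures are for assumed correlations of 0.3, 0.5 and 0.7, with SD 4 at both times and 88 evaluable patients per arm. The article does not settle which case applies, so neither an inflated error nor a loss of power is shown to be what will happen. The deciding estimate still needs to be fixed before the data are seen, because it carries the trial's main conclusion in an open-label comparison.

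**What to change.** Replace the ANOVA sentence with wording such as the following.

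*The primary analysis estimates the TMC minus control difference in mean 12-month ESS by ANCOVA (or an equivalent mixed model), adjusted for baseline ESS and randomisation stratum. Non-inferiority is concluded if the one-sided 95% confidence limit for this difference, in the direction of worse sleepiness, excludes the 1.5-point margin. It is not judged on a group main effect averaged over baseline and follow-up, nor on a non-significant F-test.*

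Baseline ESS then enters as a covariate and not as an outcome on which the arms are compared. The change is to wording only, in the protocol or the SAP. It needs no new data, no more patients and no change to the 88 per arm.

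### Randomisation is stratified by three groups, but the primary ANOVA as stated has no stratum term; adding one would sharpen the non-inferiority limit at almost no cost

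*Protocol article*

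**What the plan says.** In the protocol article, under Population, intervention and procedures of the tele-multidisciplinary care (TMC) study, allocation is 1:1 from a list "stratified for three groups: children, adults with incident condition, adults with prevalent condition".

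Under Sample size and statistical considerations of the same study, "A total of 176 patients (88 per arm) are required" to show that the "95% lower limit of one-sided CI" lies "above the non-inferiority limit of − 1.5 ESS points difference (standard deviation of 4), with 80% of power". On the source of the SD it states: "The standard deviation value (±4) was based on the Italian validation study of ESS [28".

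The primary method is given in one sentence: "Repeated measures ANOVA will be used to compare EDS between groups at baseline and after 1-yr of follow-up". Group and time are the only factors named. The strata are neither listed as model terms nor expressly left out.

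**The concern.** The strata could plausibly differ in the course of ESS over 12 months. Incident adults enter shortly after diagnosis, while prevalent adults have an established diagnosis. Table 1 gives adolescents a different instrument (ESS-CHAD) and follows incident and prevalent patients on different schedules.

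Stratified allocation balances the arms within each stratum, so differences between strata drop out of the true sampling error of the arm comparison. A model without the strata still counts those differences as residual variance. Its standard error is then larger than the one the design delivers, and the one-sided limit lies further out than the data require. At stake is precision in a trial planned at only 80% power: a televisit arm that is truly non-inferior would miss the margin somewhat more often than it needs to.

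**Working it through.** **Inputs from the protocol article (TMC sample size section):** margin 1.5 ESS points, SD 4, one-sided 5%, power 80%, 88 evaluable per arm. **Assumptions:** true arm difference zero for power; the same arm effect in every stratum; 4 is the total SD of the quantity analysed; R² is the share of that variance lying between strata, not given in the documents and varied from 0 to 0.20.

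**1. The plan's own figure.** n per arm = 2(z₀.₉₅ + z₀.₈₀)² × SD² / margin² = 2 × (1.6449 + 0.8416)² × 16 / 2.25 = 87.9, so 88 per arm and 176 in total. This matches. One-sided 2.5% would need 112 per arm (224), so one-sided 5% is the basis. The formula is a plain two-arm comparison with no strata.

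**2. Which stratum differences matter.** With two time points, the arm-by-time test is a comparison of mean change. A constant offset between strata, for example from a different instrument, cancels. Only differences between strata in 12-month change stay in the residual. For the same reason, a stratum main effect alone would not reduce the error of the arm-by-time contrast; stratum-by-time is needed.

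**3. With and without the strata, 88 per arm.**
- Model SE without strata: 4 × √(2/88) = 0.603; one-sided half-width 1.6449 × 0.603 = 0.992.
- True SE under stratified allocation: 0.603 × √(1 − R²).
- Power without strata: Φ[(1.5 − 0.992) / true SE].
- Power with strata: Φ[1.5 / true SE − 1.6449].
- True type I error without strata: 1 − Φ[0.992 / true SE].

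| Assumed R² | Half-width with strata | Power without strata | Power with strata | Type I error without strata |
|---|---|---|---|---|
| 0 | 0.992 | 80.0% | 80.0% | 5.0% |
| 0.05 | 0.967 | 80.6% | 81.8% | 4.6% |
| 0.10 | 0.941 | 81.3% | 83.6% | 4.2% |
| 0.20 | 0.887 | 82.7% | 87.2% | 3.3% |

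The half-width without strata is 0.992 in every row. At R² = 0.10 that is about 5% wider than needed (0.992 / 0.941 = 1.05), and at 0.20 about 12% (0.992 / 0.887 = 1.12).

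**4. What such an R² means in ESS points.** Suppose one stratum holds a quarter of the patients and its mean change differs by d from the rest. The between-stratum variance is 0.25 × 0.75 × d². For d = 2, 3 and 4 this is 0.75, 1.69 and 3.0, so R² = 0.05, 0.11 and 0.19 after division by 16. The quarter share is illustrative.

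**5. The other reading of the SD.** Take 4 as the within-stratum SD of change, with two equal strata differing by d in mean change. The model SD is then √(16 + 0.25d²), which is 4.12, 4.47 and 5.0 for d = 2, 4 and 6. Power without strata is Φ(1.5/0.603 − 1.6449 × model SD/4) = 78.6%, 74.2% and 66.7%, with type I error 4.5%, 3.3% and 2.0%. With strata, power returns to about 80% and type I error to about 5%. If 4 is the total SD, the same d = 4 leaves a within-stratum variance of 16 − 4 = 12, and power is 83.5% without the strata and 89.0% with them.

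**The case against.** The strongest objection is that the point reads too much into one sentence. The source is a condensed journal article; the full protocol and any SAP are not shown, and covariates are commonly settled there. The sentence does not say that the strata are excluded, so a reader who infers that they will be left out goes beyond the text. This stands, and limits the point to the method as it is written. A concrete improvement to a stated method can still be recommended.

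A reader might also infer that leaving out the strata costs the trial its stated 80% power. The documents do not support that. The 80% was computed for an unadjusted comparison with SD 4, and with 4 as the total SD the unadjusted power never falls below it. The figures below 80% in step 5 arise only if 4 is a within-stratum SD of change, and the article does not describe it so. In fairness, Table 1 assigns the cited ESS reference to adults only, and nothing says that 4 is an SD of change in this mixed population, so that reading cannot be ruled out. It is not the stated one, however, and it measures the loss against a more variable population than the plan assumed.

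Two further objections stand. Stable differences between strata cancel in the arm-by-time contrast, so only differential change counts, and the documents give no size for it. And the error is in the safe direction: true type I error is at or below 5%, so the omission cannot raise the risk of a false non-inferiority claim.

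**Conclusion.** The point holds as a modest improvement. The randomisation is stratified and the primary model, followed as written, does not use the strata. If the strata differ in 12-month ESS change, the limit is conservative and some power is forgone: from nothing at R² = 0 to about 4.5 percentage points at R² = 0.20 (82.7% against 87.2%). This rests on 4 being the total SD of the analysed quantity, on equal arm effects across strata, and on an R² range that is assumed. On the same basis the stated 80% power is met with or without the strata. The mechanism is certain; its size in this trial cannot be determined from the documents.

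**What to change.** In Sample size and statistical considerations of the TMC study, add one sentence stating that the primary model includes the three randomisation strata and that the one-sided 95% limit for the arm difference is taken from that model. If the repeated measures ANOVA is kept, enter stratum-by-time; if 12-month ESS is modelled directly, a stratum factor is enough. If the full protocol or SAP already specifies this, confirming it is sufficient.

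For the arm-by-time contrast, three strata use 2 degrees of freedom, leaving 172 instead of 174 with 176 patients. No further patients or data are needed, and the sample size can stay as it is.
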